## Discussion

Over a 2 year period the 'Physical Activity at Home' study will test the effectiveness, in terms of long term physical activity adherence, health benefits and cost, of a physiotherapy-led home based physical activity program. Specifically it will target middle aged adults who are less likely to adopt and maintain physical activity, as they do not access the currently available community group exercise programs. With few studies reporting on the long term adherence to physical activity post intervention and no known studies reporting on targeted physical activity interventions for those not interested in group or centre based programs, if this program is successful it could allow more individuals to increase their physical activity levels towards that needed to achieve the associated health benefits.

One of the strengths of this trial is that the inclusion criteria are broad proposing that there is some benefit from physical activity for almost everyone [42]. The recruitment method also attempts to minimize self-selection and recruitment of highly motivated volunteers by using the electoral roll, allowing a more representative sample [24]. Phone coverage is widespread in Australia therefore recruitment and providing the home based intervention via this method should also limit selection bias. All measurements will be performed by the same person and the sample size to be recruited should provide adequate statistical power to detect a significant difference in the main outcome measure.

A limitation of this study is the lack of randomisation to the group and home based interventions limiting the ability to attribute outcomes to treatment for all three groups. There is also a lack of blinding, as the principal researcher will be conducting all assessments and providing the home based intervention. Another possible limitation is the type of personnel conducting the interventions is not standardised, that is, a physiotherapist as compared to a fitness instructor.

If successful, this physiotherapy-led home based physical activity program should improve physical activity levels over the longer term, possibly in a cost-effective manner and particularly for those individuals who are not interested in, or unable to access, group exercise programs. This program could provide an alternative option for physical activity program delivery to sections of the population with various risk factors and/or diseases, a wider age range and across a number of different settings, such as rural and remote.

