**Discussion:**

The planned 18 month follow-up post intervention will provide an indication of the effectiveness of the group and home based interventions in terms of adherence to physical activity, health benefits and cost. If the physiotherapy-led home based physical activity program is successful it could provide an alternative option for physical activity program delivery across a number of settings.

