### Intervention

(i) Home-based intervention

Assessments for the home based program in this study will be conducted in participant's homes eliminating a number of barriers to physical activity adoption as discussed earlier [24]. Participants will be encouraged to invite a support person to attend during their initial assessment. After baseline measures are completed motivational interviewing will be used to devise an individual physical activity program [25]. A physiotherapist will discuss type, frequency, intensity, duration, benefits, barriers, goals, self-monitoring and progression of physical activity, aiming to achieve 30 min of moderate intensity physical activity most days of the week. Participants will be contacted by a physiotherapist via phone providing advice and support 2 weeks after the initial assessment and then monthly over a 6 month period, a total of approximately 6 phone calls.

(ii) Usual Care

Participants randomised to usual care will be visited by the physiotherapist in their homes. Baseline measures for the study will be completed giving participants an indication of their fitness and health status. Participants will receive two brochures 'An active way to better health. National Physical Activity Guidelines for Adults' and 'Dietary Guidelines for Australian Adults' from the Department of Health and Ageing [26,27]. They will not receive any other advice or support for increasing exercise or physical activity levels.

(iii) Group exercise program

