Participants in the group based program will attend the YMCA for their baseline measures. Baseline measures will be conducted by the same physiotherapist as the home based interventions. Participants will then have a choice of times for the group based exercise program which will be during business hours replicating similar programs and times offered in this community setting. These sessions will be run by a YMCA fitness instructor at the YMCA once a week, for 60 min, over 6 months. The exercise program will involve upper and lower body strengthening exercises, gross motor skill training and aerobic fitness training. The exercise specifics will be at the discretion of the YMCA fitness instructor, with no involvement from the physiotherapist, aiming to mimic 'usual practice'. Participants will be encouraged to increase their physical activity slowly and gradually in whichever way they prefer outside of the group sessions by the YMCA fitness instructors, aiming to achieve 30 min of moderate intensity physical activity most days of the week. An individual home based exercise program will not specifically be designed for this group.

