### Outcome measures

The methods of participant assessment have been carefully considered as assessments are taking place in people's homes. All study measures will be assessed at baseline, 6, 12, 18 and 24 months.

The main outcome measure of this study is long term adherence to physical activity. Adherence will be measured using exercise diaries completed over the 2 year study period, a continuous measure. Exercise diaries have been found to be both reliable and valid [28]. Participants will be encouraged to record date, type, duration and intensity, using the modified Borg rating of perceived exertion scale (RPE) [29], every time they are physically active. Participants will be encouraged to return the diaries in the supplied prepaid envelope at the end of each month over the study period.

Average monthly adherence rates across the 2 year period will be calculated as follows: number of physical activity sessions reported as a percentage of physical activity sessions prescribed for the month. This is similar to the method described by King [20] to determine adherence rates to different physical activity intensities and formats over a 2 year period. The number of sessions prescribed for the month will be based on the World Health Organisation (WHO) physical activity guidelines [3]. That is, 30 min of moderate intensity physical activity, five or more days per week, a total of 20 or more sessions per month. Thirty minutes can be accumulated in 10 min bouts of physical activity per day. Moderate intensity is defined as a rating of 3 or more on the modified Borg RPE scale.

Secondary outcomes include the Active Australia Survey (AAS), accelerometry, aerobic capacity (2 min step test), quality of life (SF-12v2) and disease biomarkers, that is, waist circumference (cm), waist:hip ratio (WHR), blood pressure (mmHg) and body mass index (BMI, kg/m^2^).

The AAS and accelerometry will be used to validate the data collected from the exercise diaries. These two continuous measures will be collected every 6 months over the 2 year study period.

The AAS has been designed to measure participation in leisure time physical activity and to assess the participant's knowledge of current public health messages about the health benefits of physical activity. It offers a short and reliable set of questions and applies to 1 week preceding the interview, including walking for transport. The AAS has been reported as reliable and of acceptable validity [30,31].

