Covering the same time period as the AAS, participants will wear an Actigraph GT1M accelerometer [32] for 7 consecutive days. Accelerometers allow an objective measurement of quantity and intensity of movement and have been found to be reliable and valid [33].

The raw data collected by the accelerometer, counts, will be used to obtain the time spent in different physical activity intensities [34]. We will use the Freedson Combination energy expenditure algorithm to determine the intensity cut-points [32]. This outcome variable will be used to investigate whether participants have reached the WHO physical activity guidelines.

Assessment of aerobic capacity is essential to determine whether the completed physical activity has been intense enough to result in an improvement in cardiovascular fitness. The 2 min step test requires little space and equipment, with large studies finding it both reliable and valid [35]. The 2-minute step test protocol involves determining the number of times in 2 min that a person can step in place raising the knees to a height halfway between the patella (kneecap) and iliac crest (front hip bone), a continuous measurement. Only one successful trial will be administered.

The SF-12v2 is a general health status questionnaire which has a 12-item scale producing eight separate sub-scales (physical functioning, physical role functioning, emotional role functioning, social functioning, bodily pain, mental health, vitality and general health perceptions) to assess quality of life [36]. It takes the participant less than 2 min to complete the tool and is a quasi-continuous measurement.

Waist circumference and hip circumference will be measured in centimetres using a tape measure. Blood pressure levels will be obtained using a mercury sphygmomanometer on the right arm of seated subjects. Both measures will be taken twice and then the average will be recorded. BMI (kg/m^2^) will be recorded using a portable set of scales and a stadiometer.

Sociodemographic information will also be collected with questions regarding participant's education level, relationship status, current employment status and the presence of any chronic diseases.

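### The unblinded provider of the home program also takes the observer-dependent secondary outcomes (blood pressure, tape measures, step test), and no stated safeguard removes bias that differs by arm

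*Protocol article*

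**What the plan says.** The protocol article's Discussion describes the measurement arrangement twice. The paragraph that opens "One of the strengths of this trial is that the inclusion criteria are broad" goes on to say: "All measurements will be performed by the same person". The following paragraph, on limitations, says: "There is also a lack of blinding, as the principal researcher will be conducting all assessments and providing the home based intervention".

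The Intervention section fits this. For usual care: "Participants randomised to usual care will be visited by the physiotherapist in their homes". For the group program: "Baseline measures will be conducted by the same physiotherapist as the home based interventions".

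The Outcome measures section fixes the methods:

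- **Blood pressure:** "Blood pressure levels will be obtained using a mercury sphygmomanometer on the right arm of seated subjects".
- **Waist and hip:** by tape. Blood pressure and tape measures are each taken twice and averaged.
- **Step test:** a count of knee raises to a set height over 2 minutes, with one successful trial.
- **Active Australia Survey:** it "applies to 1 week preceding the interview, including walking for transport". The article does not say who conducts that interview.
- **Primary outcome:** an exercise diary that participants fill in and post back monthly.
- **SF-12v2 and accelerometry:** the first is completed by the participant. The second is a seven-day recording that the article calls objective.

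**The concern.** The person who reads blood pressure, places the tape and counts steps knows each participant's program and has delivered one of the programs being compared. In such measures the observer influences the recorded value: where the column is read, how tightly the tape is drawn, which knee raises count, and how much encouragement is given. A small tendency that differs by arm goes straight into the difference between arms.

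Randomisation does not protect against this, because the tendency arises after allocation. The randomised home versus usual care comparison of these outcomes is therefore exposed. So is the third hypothesis, that the home program's health benefits match those of the group program, because a tendency favouring home could hide a shortfall.

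Naming the single assessor among the strengths obscures the point. It is a strength for reproducibility between visits and participants, but not for bias by arm.

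**Working it through.** **1. Which outcomes the observer can influence** (Outcome measures section)

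| Outcome | How the value arises | Open to the observer? |
|---|---|---|
| Diary adherence (primary) | participant writes, posts monthly | not an observer reading |
| Accelerometry | device | not an observer reading |
| SF-12v2 | participant completes | not an observer reading |
| BMI | scales and stadiometer | little |
| Blood pressure | mercury column read by the assessor | yes |
| Waist, hip, waist-to-hip ratio | hand tape | yes |
| Step test | counted to a height criterion, one trial | yes |
| Active Australia Survey | called an interview, interviewer not named | unclear |

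**2. Whether the stated safeguard helps.** Write one reading as true value + b(arm) + random error. The mean of two readings is true value + b(arm) + half the sum of the two errors. The error variance is halved and b(arm) is unchanged. Averaging does nothing about a tendency that differs by arm, and neither does having one assessor.

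**3. Number per arm for the illustration.** The Sample size section gives a difference of 20, an SD of 35, power 0.8, 25% dropout and 64 per group. With two-sided alpha 0.05:

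n = 2 × [35 × (1.960 + 0.842) / 20]² = 48.07, and 48 / 0.75 = 64.

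The stated figure is reproduced, and 48 completers per arm is the plan's own expectation. (Rounding 48.07 up to 49 first would give 66, which is immaterial here.)

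**4. Effect of an arm-dependent difference b when there is no true effect.** The documents give neither an SD for systolic pressure nor a size for b. Both are assumptions.

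SE = SD × √(2/48), and P(significant) = Φ(b/SE − 1.96) + Φ(−b/SE − 1.96).

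| Assumed SD (mmHg) | SE | b = 2 mmHg | b = 3 mmHg |
|---|---|---|---|
| 12 | 2.45 | 12.9% | 23.2% |
| 15 | 3.06 | 10.0% | 16.5% |
| 18 | 3.67 | 8.5% | 12.9% |

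The nominal rate is 5%. Nearly all of the excess falls in the direction of b: for SD 12 and b = 2, 12.6 of the 12.9 percentage points.

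**5. Effect of baseline adjustment.** The primary analysis adjusts for baseline, which reduces the SE. If b is present only at follow-up, the inflation is then larger than shown. If a similar difference were already present at baseline, adjustment would remove part of it. The figures above are for an unadjusted comparison at one visit.

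**The case against.** The strongest reply is that the authors have already said this. The limitations paragraph names the dual role and the lack of blinding, and a pragmatic trial with one researcher may have no second assessor. That is fair, and a reader who infers from the strengths paragraph that the problem was overlooked or hidden would be wrong. But disclosure does not change the readings, and the methods chosen leave more to the observer than they need to, at least for blood pressure.

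Four stronger readings are tempting, and the document does not support them.

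- **That every outcome is observer-dependent.** The wording about all assessments invites this, but the primary diary, the SF-12v2 and accelerometry are not read by the assessor. The fourth hypothesis, on long-term activity, rests mainly on the diary.
- **That home participants report their activity to their own coach.** The word interview describes the survey's recall window. No one is named as interviewer, and the cost-effectiveness section refers to six-monthly questionnaires.
- **That follow-up is not free of coaching in the home arm.** The abstract says "The planned 18 month follow-up post intervention will provide an indication of the effectiveness of the group and home based interventions", and support is described as about six calls over six months. Nothing describes coaching at the later visits, and usual care is visited at home by the physiotherapist too. Only the prior relationship differs.
- **That the bias would occur.** The document gives no size or direction for it, and an average shift of 2 mmHg over a whole arm is a supposition.

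Two steps in the point itself are also inferred. That the principal researcher is the physiotherapist follows from reading the Intervention and Discussion sections together. That this person measures the group arm at follow-up follows from the general statements in the Discussion, since the Intervention section says so only for baseline.

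**Conclusion.** The point holds for blood pressure, waist and hip measures and the step test. These secondary outcomes are taken with observer-dependent methods by the unblinded provider of one arm, and no described safeguard acts on bias that differs by arm. It does not reach the primary outcome directly. The two statements in the Discussion can both stand only if the first is confined to variation between observers.

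The size is known only under assumptions. With 48 completers per arm and an SD of 12 to 15 mmHg, a differential reading of 2 mmHg would roughly double the 5% error rate or somewhat more, and 3 mmHg would take it to about 17-23%. Only blood pressure has been illustrated. The calculation shows that a modest tendency could produce a false finding of benefit, not that one will arise. This merits a change because the main remedy is cheap, but it does not undermine the trial's main comparison.

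**What to change.** Four changes, none of which needs extra staff:

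1. **Outcome measures, blood pressure:** replace the mercury sphygmomanometer with a validated automated device in all arms from baseline, and average two stored readings. This is the most useful change, because it takes the reading out of the observer's hands.
2. **Outcome measures, Active Australia Survey:** state that it is self-completed before the visit in all arms. This settles the open question of the interviewer and protects one of the two checks on the diary data.
3. **Outcome measures, tape and step test:** state that earlier results are not available to the assessor when these are taken. This does not blind the assessor to the arm, but it removes the participant's previous value as a target.
4. **Discussion:** limit the same-person statement to reduced variation between observers, and refer to the limitation that follows it.

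The cost is one device and probably slightly more missing survey items. If anyone has already been measured with the mercury device, record the device used at each visit. The SF-12v2 needs no change, since it is already described as participant-completed.

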## Ethical approval

This trial was approved by the University of Canberra Committee for Ethics in Human Research in November 2009 (Project number 09-97).
